#### Inclusion criteria

The inclusion and exclusion criteria reflect patients who are at high risk of hospital readmission after hospital discharge (see [19] for a detailed account of previously published research identifying risk factors for readmission). Participants are included in the trial if the following criteria are met:

• aged 65 years and over,

• admitted with a medical diagnosis (i.e. non-surgical),

• able to speak and understand English, and

• have at least one of the following risk factors for readmissions: - aged 75 years or older,

- hospital admission/s in the previous 6 months to this admission,

- multiple comorbidities (2 or more),

- lives alone,

- lacks social support,

- fair or poor self-rating of health,

- moderate to severe functional impairment, and/or

- history of depression.

#### Exclusion criteria

Participants are excluded from participating in the trial if the following criteria are met:

• they require home oxygen,

• are dependent on a wheelchair or unable to walk independently for 3 meters (patients independently using walking aids are included),

• live in a nursing home (i.e. high dependency unit; patients living in independent hostel or retirement village accommodation are included), or

• have a progressive neurological or cognitive deficit or disease.

#### Randomisation

Participants consenting to participate are randomly allocated into one of the four trial groups after the baseline assessment is completed. A randomisation master list was generated by the project coordinator via a computer-generated randomisation algorithm prior to commencement of recruitment.

#### Sample size

A total of 328 participants (82/group) is aimed to be recruited. Based on our previous research in the area [19] it is anticipated that there will be approximately 25% attrition (20/group) over 6 months of follow-up for reasons such as death, changing mind about participating, or moving away. A sample of 62 completing participants per group (82-20 = 62) is required to detect a 4 week difference in time to hospital readmission. This sample size was determined by power analysis and based on an expected difference in median time to readmission between groups over 24 weeks. Significance level (alpha) was established at 0.05 to avoid a Type 1 error, and power (1 - beta) was set at 90% to avoid a Type II error. Therefore, for a 90% chance of detecting as significant a 4 week difference in time to hospital re-admission, 62 patients in each group are needed to complete the study.

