#### Primary and secondary analysis

All data analyses will be conducted based on the principle of intention to treat [22]. Chi square, ANOVA, and Kruskal-Wallis tests will be used for bivariate analysis. For the primary outcomes of emergency health service use, Kaplan-Meier survival curves and log rank statistic will be used to compare intervention and control groups. A Cox proportional hazards regression model will be used to determine the effect of the interventions and adjust for any potential confounding variables. A general linear model approach will be used for multivariable repeated measures analysis of covariance for continuous outcome variables (e.g. measures of functional status, quality of life and psycho-social well-being) to investigate the differences over the four data collection points. Economic data will be collected to enable a comprehensive evaluation of the cost-effectiveness of the interventions when compared to that of usual care. Mean treatment costs differentials between control and intervention groups will be calculated. The patient level data will be used alongside other routinely available data to inform a decision analytic cost-effectiveness model.

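### No rule is given for deaths before readmission; if they are censored, as the plan's wording suggests, one minus Kaplan-Meier would overstate the proportion readmitted in each arm

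*Protocol article*

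**What the plan says.** Three parts of the protocol article bear on this.

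- **Sample size.** About 25% attrition (20 of 82 per group) is expected over six months, "for reasons such as death, changing mind about participating, or moving away". The calculation is "based on an expected difference in median time to readmission between groups over 24 weeks", with a 4-week difference as the target.
- **Primary outcomes.** Time to first unplanned readmission is listed. Death is not part of the event, and mortality is not among the primary or secondary outcomes.
- **Primary and secondary analysis.** For emergency health service use, "Kaplan-Meier survival curves and log rank statistic will be used to compare intervention and control groups", followed by a Cox model, all by intention to treat.

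Under Secondary outcomes, the cost-effectiveness measures include readmissions avoided and time gained before readmission. How they are to be estimated is not said. The article states no rule for censoring at death, no death rate and no expected readmission rate.

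**The concern.** A patient who withdraws or moves away may still be readmitted unseen. A patient who has died cannot be, and that patient's readmission status is fully known. Grouping the two and then using Kaplan-Meier with a readmission-only event leads naturally to censoring at death. Dropping these patients instead would conflict with intention to treat.

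With deaths censored, one minus Kaplan-Meier estimates readmission in a hypothetical setting without death, not the proportion of patients actually readmitted. The participants are 65 or over, acutely admitted and selected for readmission risk, and death is the first reason listed for attrition, so the distinction is not academic. At stake are the absolute figures: 24-week readmission risk, median time to readmission, and any economic quantity taken from the curve.

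**Working it through.** **Inputs.** The article gives the 24-week follow-up, the readmission-only event, the methods and the attrition allowance. That allowance is consistent to rounding (82 × 0.75 = 61.5, against 62 completers; 4 × 82 = 328), but the share due to death is not stated. There is no stated readmission risk to reproduce. The readmission and death rates below are therefore assumptions, with constant hazards.

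**1. Overstatement within an arm.** Let pr be the true proportion readmitted by week 24 and pd the proportion dying first.

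- Total cumulative hazard: L = −ln(1 − pr − pd)
- Readmission part: Lr = L × pr/(pr + pd)
- One minus Kaplan-Meier with deaths censored: 1 − exp(−Lr)

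Example, 40% and 10%: L = −ln(0.50) = 0.693; Lr = 0.693 × 0.8 = 0.555; 1 − exp(−0.555) = 42.6%.

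| Readmitted (true) | Die first | 1 − KM | Excess, points |
|---|---|---|---|
| 40% | 5% | 41.2% | 1.2 |
| 40% | 10% | 42.6% | 2.6 |
| 50% | 5% | 51.6% | 1.6 |
| 50% | 10% | 53.4% | 3.4 |
| 60% | 10% | 64.4% | 4.4 |

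At 20-30% readmitted and 5% dying first, the excess is 0.6-0.9 points.

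**2. The same check with a different death input.** Here d is the 24-week risk of death ignoring readmission and F is one minus Kaplan-Meier. With Hr = −ln(1 − F) and Hd = −ln(1 − d), cumulative incidence = Hr/(Hr + Hd) × [1 − exp(−(Hr + Hd))].

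- F = 50%: 48.9% at d = 5% and 47.7% at d = 10%.
- Over F = 20-60% and d = 5-10%, the excess is 0.5-2.6 points.
- If all 25% attrition were death (an extreme), it is 3.7 points at F = 30% and 5.8 at F = 50%.

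These figures are smaller at the same nominal rate because d includes deaths that would fall after readmission. The direction is the same.

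**3. Median.** In the 50%/10% case Lr = 0.7636, so the Kaplan-Meier median is 0.693 × 24/0.7636 = 21.8 weeks. Actual readmission reaches 50% only at week 24, a shift of 2.2 weeks within an arm. The between-arm difference would move less if deaths are balanced.

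**4. Between-arm comparison.** Take one minus Kaplan-Meier of 50% (control) and 35% (intervention), a difference of 15.0 points. The cause-specific hazard ratio is ln(0.65)/ln(0.50) = 0.62 whatever the death rates. The difference in cumulative incidence by the formula in step 2 is:

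| Deaths, control / intervention | Difference, points |
|---|---|
| 5% / 5% | 14.7 |
| 10% / 10% | 14.4 |
| 10% / 5% | 13.6 |
| 5% / 10% | 15.5 |

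**5. Unequal deaths, equal readmission hazards.** With F = 50% in both arms and deaths of 5% and 15%, Kaplan-Meier shows no difference. Cumulative incidence is 48.9% and 46.6%, lower in the arm with more deaths.

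**The case against.** The strongest reply is that the article never says deaths are censored. Listing death in an attrition allowance is correct for its purpose, since a patient who dies does not complete follow-up, and a detailed censoring rule may sit in an analysis plan not available here. Nor does the article say that a 24-week risk will be read from the curve; Kaplan-Meier and log-rank are named for comparing groups. All of this stands, and it makes the point conditional. It does not remove it: the article does name a method and an event, and following them as written leads to censoring at death.

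A reader might infer three stronger things that the document does not support.

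- That the group test is invalid. It is not: log-rank and Cox compare cause-specific hazards, and step 4 shows the hazard ratio unchanged.
- That Kaplan-Meier makes an arm with more deaths look better. Under independent constant hazards extra deaths leave it unchanged; step 5 shows that the cumulative incidence curve is the one that falls.
- That readmissions avoided and time gained would be too high. Their source is not stated, and step 4 shows that a Kaplan-Meier difference can be too large or too small.

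**Conclusion.** The point holds as a conditional one about absolute figures. If deaths are censored and one minus Kaplan-Meier is reported as the 24-week readmission risk, the proportion readmitted is overstated in each arm, and a median read from the same curve comes too early. The direction is certain given those conditions. The size is about 1 to 4 points for 40-60% readmitted and 5-10% dying first, and under 1 point at 20-30% readmitted with 5% dying first. It rests on assumed rates and constant hazards. Reading the text as establishing that deaths are censored, or that a reported risk is already wrong, goes beyond it.

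The primary group comparison is unaffected. Between-arm economic quantities would be affected only if taken from the curve, and then in either direction with partial cancellation.

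**What to change.** In Primary and secondary analysis:

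- State how a death before readmission is handled, separately from withdrawal and moving away.
- Present cumulative incidence (Aalen-Johansen) curves for unplanned readmission with death as a competing event in place of one minus Kaplan-Meier. Use them for any absolute risk, timing or economic quantity.
- Keep log-rank and Cox, labelled as comparisons of the cause-specific hazard of readmission.
- Report deaths by arm and add one sensitivity analysis of time to first unplanned readmission or death. Both are needed because cumulative incidence alone can favour an arm with more deaths.

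The cost is a small amount of extra analysis. It assumes that dates of death are obtained, which the article does not state, so their collection should be confirmed.

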### Blinding

Randomisation to a trial group occurs after baseline assessment is completed, thus the hospital-based RA is initially blind to the study group. A Senior Research Assistant (SRA) is employed (off-site) to enter and collect follow-up outcomes data at 4 weeks following hospital discharge, 12 weeks following hospital discharge, and 24 weeks following hospital discharge. The SRA is blind to the participants' allocated group. An Advanced Practice Gerontic Nurse (APGN) and physiotherapists and exercise physiologist are employed to implement the interventions and it is not be possible to blind the intervention research staff to the trial condition, nor the participants to their allocated intervention.

### Study conditions

#### Usual care control group (Group 1)

Patients who are allocated to the usual care control group receive routine discharge planning and rehabilitation advice as determined by the health service. If the hospital staff identify that in-home visits or rehabilitation services are required after discharge (e.g. community nursing visits), they are organised in the routine manner.

#### Exercise and in-home/telephone follow-up intervention group (Group 2)

Patients who are allocated to the exercise and in-home/telephone follow-up intervention group will receive an intervention following a protocol designed specifically for older patients who are at high risk of poor post-discharge outcomes. The protocol provides a guide for the management and assessment of each patient during the intervention. The intervention extends from recruitment during hospital admission to 24 weeks after discharge and consists of specific patient assessment and management strategies and a schedule of contact visits by the APGN and physiotherapist or exercise physiologist. These include:

Whilst in hospital:

1. APGN, within 72 hours of admission, will visit intervention patients, undertake a health assessment, and prepare a comprehensive transitional care plan. This process includes discussing the planned discharge plan with patient's caregivers, doctor, and ward nurses to individualise the plan;

2. Physiotherapist, within 72 hours of admission, will visit the intervention patients to determine the functional capacity of the patient using measures of ADL and performance tests of balance and gait. This information will be used to plan individualised exercise programs designed to improve strength, stability, coordination, endurance, mobility, and improve self confidence with respect to ADL. The exercise prescription will be developed using a team approach involving the patient, caregivers, doctors, and ward nurses. Goals will be defined for each subject and used as a motivational strategy to improve compliance with the program;

3. Physiotherapist will provide each intervention patient with a pedometer together with simple verbal and written instructions regards usage and journaling of activity levels; and

4. APGN will visit patients 2^nd ^daily thereafter until discharge to establish and implement the program, monitor progress, and modify transitional care plan if required.

After discharge home:

5. APGN, within 48 hours post discharge, provides one in-home visit. This home visit is undertaken to 1) identify sufficient caregiver support is available at home, 2) assess the home environment is safe, 3) determine the patient has the required medications and dressings (if required), 4) ensure the patient (and caregiver) fully understand their medication and treatment regimes; 5) reinforce and further explain exercise program and use of pedometer and journal in the home, and 6) provide advice and support to the caregiver;

6. Additional in-home visits are available by APGN after discharge if required;

7. An exercise physiologist RA conducts 6 weekly in-home visits to reassess the patient's physical measures and functional capacity, evaluate progress with the exercise program, and reset program goals accordingly;

8. APGN, over the initial 4 week period post discharge, provides weekly telephone follow-up calls. Feedback is sought from patients and caregivers regarding medications and treatments and if there are any problems requiring assistance. Where difficulties arise, further advice, information, and support is offered together with reinforcement and further explanation of the exercise program;

9. APGN is available to be contacted via telephone 7 days per week. This availability allows patients and caregivers to access the APGN for further information, support, and guidance should the need arise; and

10. Monthly telephone follow-up calls continue as described above (steps 9 and 10) undertaken by the APGN for 6 months following hospital discharge.

#### Exercise only follow-up intervention group (Group 3)

Patients allocated to the exercise only follow-up intervention group will receive only the exercise component of the protocol, that is, protocol steps 1, 3, 4 and 8.

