## Methods/design

### Study design and setting

The study is a randomised controlled trial to evaluate the effectiveness of exercise-based and/or in-home telephone follow-up strategies for older patients at risk of hospital readmission. Participants are recruited from two tertiary metropolitan hospitals. After baseline data is collected, participants are randomly assigned to one of four groups, either 1) the usual care control group, 2) the exercise and in-home/telephone follow-up intervention group, 3) the exercise only intervention group, or 4) the in-home/telephone follow-up only intervention group.

The usual care control group receives usual discharge planning provided by the health service. The exercise only intervention group, in addition to usual care, receives an assessment by a physiotherapist to form the basis for an individually designed exercise plan aimed at improving functional ability. The program commences in-hospital and is followed up in-home at 6 weekly intervals for 24 weeks by an exercise physiologist. The exercise and in-home/telephone follow-up intervention group, in addition to usual care and the exercise intervention, receives an intervention from admission to 6 months post discharge including home visit/s following hospital discharge and regular telephone follow-up from a gerontology nurse for 6 months post-discharge. The in-home/telephone follow-up only group receives the in-home visits and telephone follow-up from the gerontology nurse as outlines above, with the omission of the exercise program. Participants in all groups complete assessments at baseline (within 72 hours of hospital admission), 4 weeks following hospital discharge, 12 weeks following hospital discharge and 24 weeks following hospital discharge.

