#### In-home/telephone follow-up only intervention group (Group 4)

Patients allocated to the in-home/telephone follow-up only intervention group

will receive only the APGN component of the protocol, that is, protocol steps 1, 2, 5, 6, 7, 9, 10, and 11.

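### The step numbers that define the exercise-only and nurse-only arms contradict the numbered intervention list and the arms' own descriptions

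*Protocol article*

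**What the plan says.** All references are to the protocol article. The section on Group 2, the combined arm, sets out ten steps, numbered 1 to 10 without a gap, and names who delivers each one. For example, step 2 reads "Physiotherapist, within 72 hours of admission, will visit the intervention patients to determine the functional capacity of the patient", step 7 reads "An exercise physiologist RA conducts 6 weekly in-home visits" and step 8 reads "APGN, over the initial 4 week period post discharge, provides weekly telephone follow-up calls".

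The next two sections define the single-component arms by pointing back to that list. Group 3 patients are to "receive only the exercise component of the protocol, that is, protocol steps 1, 3, 4 and 8". Group 4 patients "will receive only the APGN component of the protocol, that is, protocol steps 1, 2, 5, 6, 7, 9, 10, and 11".

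The list also refers to itself. Step 10 begins "Monthly telephone follow-up calls continue as described above (steps 9 and 10", so one of the two steps it points up to is step 10.

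Two other places describe the arms in words. The Abstract (Methods/Design) says that each single-component arm gets only its own component. Study design and setting gives Group 3 a physiotherapist's assessment, an individual exercise plan and home follow-up by an exercise physiologist every six weeks. It gives Group 4 the nurse's home visits and calls "with the omission of the exercise program".

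**The concern.** Each of the two sentences states an arm's content twice, once in words and once in numbers, and the two statements disagree. Followed by number, the exercise-only arm would get nurse contacts without the exercise assessment or the exercise-physiologist visits, and the nurse-only arm would get both of those exercise elements.

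This matters because of what the two arms are for. The Discussion says that the team's previous trial could not separate the components of its multi-faceted intervention, and that this trial extends that work. Groups 3 and 4 make the separation possible. The two step lists are also the article's only step-level definition of those arms. Anyone judging fidelity, replicating an arm or reading the component contrasts has to use them, and as printed they cannot be applied.

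**Working it through.** No sample-size, power or alpha figure is involved. The check sets the ten-step list beside the two arm lists.

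**1. Classify each step by its named provider, and mark where it is cited.**

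| Step | Content, in brief | Provider | Cited for Group 3 | Cited for Group 4 |
|---|---|---|---|---|
| 1 | Health assessment and care plan | Nurse | yes | yes |
| 2 | Functional assessment, exercise planning | Physiotherapist | no | yes |
| 3 | Pedometer and journal | Physiotherapist | yes | no |
| 4 | Ward visits until discharge | Nurse | yes | no |
| 5 | Early home visit | Nurse | no | yes |
| 6 | Further home visits if needed | Nurse | no | yes |
| 7 | Six-weekly home reassessment | Exercise physiologist | no | yes |
| 8 | Weekly calls | Nurse | yes | no |
| 9 | Telephone availability | Nurse | no | yes |
| 10 | Monthly calls | Nurse | no | yes |
| 11 | Not in the list | none | no | yes |

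The exercise set is {2, 3, 7}, three steps. The nurse set is {1, 4, 5, 6, 8, 9, 10}, seven steps.

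**2. Compare the arm lists with these sets.**

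- Group 3 is given {1, 3, 4, 8}. Only step 3 is an exercise step, so 1 of 3. Steps 1, 4 and 8 are nurse steps. Exercise steps 2 and 7 are absent, although Study design and setting says the arm receives both.
- Group 4 is given {1, 2, 5, 6, 7, 9, 10, 11}. Steps 1, 5, 6, 9 and 10 are nurse steps, so 5 of 7. Steps 2 and 7 are exercise steps, so 2 of 3. Nurse steps 4 and 8 are absent. Step 11 does not exist.

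**3. Test a shift of one as the explanation.**

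- Group 3 without its leading 1: {3, 4, 8} − 1 = {2, 3, 7}. This is exactly the exercise set.
- Group 4 without its leading 1: {2, 5, 6, 7, 9, 10, 11} − 1 = {1, 4, 5, 6, 8, 9, 10}. This is exactly the nurse set.
- Step 10's internal reference: 9 and 10 become 8 and 9, the weekly calls and the telephone availability. The self-reference disappears.

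**4. See what the shift leaves over.** The 1 at the head of both lists would become step 0, which has no counterpart. Together the two lists use each number from 2 to 11 once and the number 1 twice. That is what an eleven-step list with a first step common to both arms would produce, but the article describes no such step. This is an inference from the pattern and is not stated anywhere.

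**5. Check whether corrected numbers would settle the matter.** Not entirely. Step 5 has the nurse explain and reinforce the exercise program, pedometer and journal, and step 8 again includes reinforcement of the exercise program. After the shift both steps belong to Group 4, the arm described "with the omission of the exercise program".

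**The case against.** The strongest reply is that this is a clerical slip and the article already says what it means. The Abstract and Study design and setting both describe the split in words, and the sentences that carry the wrong numbers also name the component. Nearly every step opens with its provider. The shift of one recovers both sets, and step 10's self-reference is another symptom of the same slip. Staff may never have worked from this article: Background says that delivery was already under way when it was written, and Intervention integrity says that the intervention protocol is documented. That working document is not shown. Nobody could follow the numbers literally, since one of them does not exist.

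Most of this stands. The intended split is clear in outline, and the cause is probably renumbering. A reader might still infer that Groups 3 and 4 received the wrong components, that 82 + 82 = 164 of the 328 planned participants are affected, or that the component contrasts are already uninterpretable. The article supports none of these. It contains no evidence about delivery, 164 is only the planned size of two arms, and the combined arm's comparison with usual care does not depend on these lists.

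On the exercise wording in steps 5 and 8, the reply is that both were written for the combined arm, and that with no exercise program in Group 4 there is nothing to reinforce. That answers part of the point and makes it secondary. The article does not say that those parts of the steps are dropped.

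The reply does not account for the leading 1, which a reader cannot resolve, and it does not supply a usable step-level definition of two of the four arms.

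**Conclusion.** The point holds as an internal contradiction in the definition of two of the four arms. Both step lists conflict with the numbered list, with the words of their own sentences and with the two prose descriptions. A renumbering error explains nearly all of it. The shared leading 1 remains unexplained, and the exercise wording in steps 5 and 8 is a smaller conflict that the prose only partly resolves.

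The size is conditional. If the numbers were followed in practice, each single-component arm (82 planned) would have received elements of the other component and missed elements of its own, and the comparison of exercise with nurse follow-up would be contaminated in both arms. If delivery followed the prose, the damage is confined to the text. The article does not show which of these happened.

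The conclusion rests on classifying steps by the provider that each one names. Step 4 mentions a program without saying which one, so its content could be argued. Steps 1, 2, 7, 8 and 11 are enough to establish the contradiction without it. Sample size, power, alpha, outcomes and analysis methods are untouched.

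**What to change.** - Reconcile the Group 2 list, the Group 3 and Group 4 step lists and the cross-reference inside step 10 with each other, and with the arm descriptions in the Abstract and in Study design and setting. Which content is correct is for the sponsor to state.
- Identify each arm's components by name as well as, or instead of, by number, so that a later change to the list cannot alter an arm.
- Say what the leading 1 in both lists refers to: a step common to both arms, or an error.
- Reconcile the exercise-reinforcement wording in steps 5 and 8 with Group 4's description, and state how those parts are handled in that arm.
- Because delivery is under way, confirm from existing contact and adherence records which components Groups 3 and 4 received, and report this with the results. Intervention Implementation says that adherence is recorded at follow-up visits and calls. Whether comparable records exist for the in-hospital steps is an assumption that the sponsor should check.

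The cost is a text correction and a review of records already held. No new data, participants or analyses are needed.
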